### Eligibility and recruitment

Pregnant women who have started prenatal care at the Health Units selected will be identified regarding their eligibility potential through access to the information system of the municipal Health Department (*HygiaWeb*). Those potentially eligible will be approached by the interviewer at the time of the prenatal consultation. Women aged ≥18 years, gestational age (GA) up to 15 weeks and 6 days, pre-gestational body mass index (BMI) between 25.0 and 29.9 kg/m2 will be included. Pregnant women who report previous diabetes (or use of oral hypoglycaemic medication and/or insulin) and use of weight loss medications will be excluded. The original study protocol intended to exclude women in twin pregnancies, however, at the time of screening most of them will not have had access to the first ultrasound result.

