### Outcomes

The primary outcome of the study is adequacy of weight gain. Weight measurements will be performed by trained nutritionists in the first and second study evaluations using a portable digital scale (Tanita®, model HS 302).

The measurement made by the nutritionists up to the 13th GW will be considered as the pre-gestational weight. For the women in the 14th GW included in the study, a value of 0.45 kg will be subtracted from the measured weight and for the women in the 15th GW included in the study a value of 0.91 kg will be subtracted from their measured weight. The results of these calculations will be adopted as an estimate of pre-gestational weight. The weight measured in the second study evaluation, preferably between the 34th and 36th GW, will be considered for the calculation of weight gain, rather than the weight measured at the moment of delivery. These procedures will be adopted due to the limitations regarding the use of self-reported pre-gestational weight and due to the high variability of water retention in the late gestation period, as well as the variability of the gestational age at delivery [28].

Weight data will be obtained from all the prenatal consultations. The mean weekly weight gain will be estimated through the difference between the weight measured in the second evaluation and the first weight recorded in the second trimester of pregnancy, divided by the number of days between the evaluation dates, divided by 7. The women with mean weekly weight gain between 0.23 and 0.33 kg in the second and third trimesters of the pregnancy will be considered to present appropriate weight gain. Insufficient weight gain will be considered for those with a mean weekly weight gain of less than 0.22 kg and excessive weight gain for women with weekly weight gain of more than 0.34 kg [23].

Secondary outcomes will be: mean weekly weight gain, changes in food intake, physical activity and the biochemical profile of the pregnant women (fasting glucose, fasting insulin, total cholesterol and fractions, triglycerides and C-reactive protein), complications in the pregnancy (gestational diabetes mellitus, hypertensive disorders and prematurity), birth weight, neonatal adiposity, weight and length/height of children at 6, 12 and 24 months of age.

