### Data collection methods

The pregnant women of both groups will undergo two evaluations in the Health Units during the pregnancy, at the time of the usual prenatal consultation. The first assessment (baseline) will be conducted prior to the 16th gestational week (GW) and the second assessment will preferably take place between the 34th and 36th GW. The third evaluation of the study comprises the analysis of the mother-child binomial. The approach in the third evaluation of the study will preferably be made at the time of the Heel Prick Test, between the third and fifth day of life of the newborn. If this is not possible, the third evaluation will be conducted at the postpartum consultation (maximum 10 days postpartum) or at the first childcare consultation (within 15 days of life). In addition, secondary data on the puerpera and the newborn will be collected from electronic medical records (*SisprenatalWeb*, *Floresce uma Vida* and *HygiaWeb*).

Study data will be collected and managed using the REDCap electronic data capture tools hosted at the Ribeirão Preto Medical School, University of São Paulo [43, 44]. REDCap is a secure, web-based software platform designed to support data capture for research studies, providing 1) an intuitive interface for validated data capture; 2) audit trails for tracking data manipulation and export procedures; 3) automated export procedures for seamless data downloads to common statistical packages; and 4) procedures for data integration and interoperability with external sources.

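### The weekly-gain formula behind the primary outcome does not tie its time interval to the two weights it subtracts; on the article's ordinary use of the word evaluation, the rate is understated for first-trimester entrants

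*Protocol article*

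**What the plan says.** The Outcomes section of the protocol article gives the rule in one sentence. The weight change is "the difference between the weight measured in the second evaluation and the first weight recorded in the second trimester of pregnancy". That change is then "divided by the number of days between the evaluation dates, divided by 7". The dates are not defined further.

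Four other statements bear on how the rule works:

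- Source of the start weight (Outcomes): "Weight data will be obtained from all the prenatal consultations". The first second-trimester weight therefore need not be a study-visit weight.
- Use of the word evaluation (Outcomes): "Weight measurements will be performed by trained nutritionists in the first and second study evaluations".
- Timing of the visits: women are eligible at "gestational age (GA) up to 15 weeks and 6 days" (Eligibility and recruitment), with no lower limit. Data collection methods places the first of two pregnancy evaluations before week 16, and "the second assessment will preferably take place between the 34th and 36th GW".
- Classes (Outcomes): 0.23 to 0.33 kg/week in the second and third trimesters is appropriate, below 0.22 is insufficient and above 0.34 is excessive.

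First-trimester entry is foreseen, because Outcomes has a separate rule for study weights taken up to week 13.

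**The concern.** A rate is correct only if its denominator is the time over which the numerator accrued. Here the numerator starts at a second-trimester weight. The denominator, if it runs between the two study evaluations, starts at a visit that may be weeks earlier. Those extra weeks add time but no counted gain, so a positive rate comes out too low.

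The result feeds the primary outcome directly, since it decides which of three classes a woman falls in, and the appropriate band is only 0.10 kg/week wide. It is also the first-listed secondary outcome. Because appropriate is a middle class, a common downward factor does not merely rescale the result. It moves some women from excessive into appropriate and others from appropriate into insufficient. The two arms can be affected in different proportions even though the rule is the same for both.

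**Working it through.** The article gives no worked value of the formula, so there is no figure of its own to reproduce. The planned sample size does not depend on this point.

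**Step 1: the factor.** Let *E1* and *E2* be the gestational weeks of the first and second study evaluations, and *W* the week of the start weight. For a given woman,

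recorded rate / rate between the two weights = (*E2* − *W*) / (*E2* − *E1*).

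This is exact and needs no assumption about the pattern of gain. It equals 1 only when *W* = *E1*. The article bounds *E1* (before 16) and *E2* (preferably 34 to 36). The values of *E1* and *W* below are assumptions, with *E2* = 35.

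| First evaluation | Start weight | Factor | Error in rate |
|---|---|---|---|
| 14 | 14 | 21/21 = 1.00 | none |
| 13 | 14 | 21/22 = 0.95 | −5% |
| 12 | 14 | 21/23 = 0.91 | −9% |
| 10 | 14 | 21/25 = 0.84 | −16% |
| 8 | 14 | 21/27 = 0.78 | −22% |
| 8 | 16 | 19/27 = 0.70 | −30% |
| 15 | 14 | 21/20 = 1.05 | +5% |

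In the last row a week-14 clinic weight precedes a week-15 first evaluation, and the error runs the other way.

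**Step 2: the classes.** Take entry at week 10 and start weight at week 14 (factor 0.84):

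- 0.38 × 0.84 = 0.32: excessive is recorded as appropriate.
- 0.25 × 0.84 = 0.21: appropriate is recorded as insufficient.
- 0.28 × 0.84 = 0.235 and 0.50 × 0.84 = 0.42: class unchanged.

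True rates above 0.34 and up to 0.34/0.84 = 0.40 leave the excessive class. True rates from 0.23 to about 0.22/0.84 = 0.26 fall into insufficient. Other women keep their class.

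**Step 3: the comparison between arms (illustrative).** The article gives no distribution of entry week, no timing of prenatal visits, and no mean or SD of weekly gain. All of these are assumed:

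- normal true gain;
- first evaluation uniform from the week shown up to week 16;
- start weight at entry if entry is in week 14 or later, otherwise uniform over weeks 14 to 18;
- second evaluation at weeks 34 to 37;
- classes split at 0.225 and 0.335, because the stated limits leave small gaps.

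Entries are relative risks of appropriate gain, intervention versus control.

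| True means (control, intervention), SD | True RR | Recorded, entry from week 7 | From week 10 | From week 12 |
|---|---|---|---|---|
| 0.42, 0.32, SD 0.10 | 2.3 | 1.2 | 1.5 | 1.7 |
| 0.40, 0.30, SD 0.15 | 1.35 | 1.01 | 1.12 | 1.20 |
| 0.40, 0.30, SD 0.20 | 1.19 | 1.0 | 1.1 | 1.1 |

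Two further runs show how far the result depends on the inputs:

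- Means 0.55 and 0.45, SD 0.15, entry from week 7: the RR falls from 2.6 to 1.8, but the risk difference rises from 9 to 12 points.
- Means 0.40 and 0.30, SD 0.15, entry at weeks 11 to 16 and next weight at weeks 14 to 16: the RR falls only from 1.35 to about 1.2, and about 9% of control women change class instead of 28%.

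**The case against.** The strongest objection is that the mismatch is inferred. The sentence does not say first and second study evaluations, a label the article often uses when it means them. It has just named two weights, and the dates could be theirs. The class limits apply to the second and third trimesters, which suits that reading better than a first-trimester start date. The word evaluation is also used more loosely elsewhere, for the educational material and for newborns.

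This stands in part: the alternative reading is open. It is not the more natural one. The same sentence uses *second evaluation* for the study visit, routine visits are called consultations, and Data collection methods counts exactly two evaluations in pregnancy. A programmer could reasonably take either reading, and the two give different primary outcomes.

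There are four stronger inferences that a reader might draw and that the article does not support:

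- *Early entrants in general are misclassified.* Only those near a class limit are, and a woman whose first evaluation supplies the start weight has no error.
- *A real benefit would be erased or reversed.* Near-complete erosion needs early entry and particular gain distributions. Reversal appears mainly when control gain is assumed already close to the band. None of these inputs is in the article.
- *The rule favours one arm.* It is the same in both.
- *Dividing by days and then by 7 is a second error.* Taken in order, 6 kg over 140 days would give 6/140/7 = 0.006 kg/week, which cannot be set against a 0.23 to 0.33 band. Days over 7 is plainly meant. If anything, this shows that the sentence is loosely drafted.

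**Conclusion.** The point holds as a defect in a stated definition. On the article's ordinary usage, the numerator and denominator of the weekly rate cover different periods whenever the start weight is not taken at the first study evaluation. For first-trimester entrants a positive rate is understated, by about 5% to 30% across the assumed cases. With an earlier clinic weight it is overstated.

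The factor itself is plain arithmetic. How many women change class, and by how much the relative risk is attenuated, rests on assumed entry weeks, visit timing and gain distributions and should be quoted only as illustration. Nothing in the article shows which reading has been implemented, so it cannot be said that any derived values are wrong. Certainty is therefore moderate. The sentence still needs correcting, because it classifies every woman for the primary outcome and should not depend on interpretation.

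**What to change.** Replace the sentence with a formula that names the dates:

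*Mean weekly gain (kg/week) = (second-evaluation weight − start weight) / [(days between the dates of those two weights) / 7].*

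Hold the date of the start weight in REDCap beside the weight, and derive the variable from those two dates. If values have already been derived, check which dates were used and recompute only those based on the study-evaluation dates.

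The cost is one sentence, one date field and one derived-variable definition. The date should be available in the prenatal record that supplies the weight. No extra visits or participants are needed.

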**Methods:**

This is a two-armed parallel randomized controlled trial that will be conducted at primary health units in Ribeirão Preto, SP, Brazil. Adult pregnant women who are overweight and receiving prenatal care in the public health system will be included. The women will be randomly allocated into control (standard care) or intervention groups. Those enrolled in the intervention group will participate in three individualized nutritional counselling sessions based on encouraging the consumption of unprocessed and minimally processed foods and the practice of physical activities. The recruitment of the participants will be carried out at seven health facilities over 12 months, with a sample of 300 women expected. Maternal anthropometric, sociodemographic, blood pressure, biochemical, and lifestyle data will be obtained at baseline (up to the 16th week of gestation), and during a second assessment (34th to 36th gestational week). The neonate body composition will be estimated after birth, and data on pregnancy outcomes, weight and height of children at 6, 12 and 24 months of age will be further obtained from medical records.

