Recent evidence suggests the importance of investigating the relationship between food consumption and health outcomes taking industrial food processing into consideration. The NOVA food classification system classifies food according to the nature, extent, and purpose of processing. Foods are categorized into four groups: unprocessed or minimally processed foods, processed culinary ingredients, processed foods, and ultra-processed food and drink products [11, 12].

Increasing the consumption of ultra-processed foods [products are made by the food industry using substances extracted from foods or obtained through chemical syntheses (i.e., soft drinks, sugar-sweetened beverages, crackers, cookies, instant noodles, flavoured yogurts, and bread with additives)] to the detriment of meal-based eating patterns consisting of fresh foods [foods that have not undergone any industrial processing (i.e., fresh fruits, beans, and fresh meats)] or minimally processed foods [foods that were processed, however, without substances added or elements removed (i.e., coffee, natural fruit juices, and pasteurized whole milk)], is considered one of the factors related to the exponential global increase in the prevalence of obesity [11, 12].

Observational studies conducted in different geographic regions suggest a direct relationship between the consumption of ultra-processed foods and obesity in adults [13–17]. In Brazilian pregnant women, it was observed that women classified in the highest tertile energy percentage (%E) from minimally processed foods had a 51% lower chance of obesity, when compared to those with lower consumption. On the other hand, a positive association between higher %E from ultra-processed foods and obesity was found [3.06 (1.27–3.37)], regardless of confounding factors [18]. In a cohort of US pregnant women, it was found that each 1% increase in %E from ultra-processed diets was associated with a 1.33 kg increase in gestational weight gain and 0.62 percentage points in neonatal adiposity [19].

Ultra-processed products have low nutritional quality, high energy density and are rich in sugar, fat and salt, characteristics that make them hyperpalatable, resulting in impaired regulation of the appetite [12, 20]. In contrast, a higher intake of unprocessed or minimally processed foods is considered a marker for the consumption of handmade meals, prepared using nutrient-balanced and satiating foods, leading to a lower chance of obesity [12, 20].

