Dietary intake will be assessed at the first and second study evaluations through two 24-h recalls on non-consecutive days in each assessment. The multiple-pass technique, performed by trained nutritionists, will be employed to obtain the recalls [29]. The Nutrition Data System for Research software, developed by the University of Minnesota in the United States, will be used to estimate the nutrients intake. Estimation of the usual diet will be carried out using the Multiple Source Method (MSM), a statistical modeling technique program developed by the European Prospective Investigation into Cancer and Nutrition (EPIC) [30]. The MSM eliminates the need for a high number of replications of the method [31] and has been found to be adequate for estimating the diet of pregnant women [32]. In addition, in the first and second evaluations of the study, the women will respond to a questionnaire on the frequency of the weekly consumption of foods of interest to assess adherence to the nutritional counselling program. The instrument used was adapted from the Surveillance System for Risk and Protection Factors for Chronic Diseases by Telephone Survey (*Sistema de Vigilância de Fatores de Risco e Proteção para Doenças Crônicas por Inquérito Telefônico* - VIGITEL) [33].

The practice of walking for leisure, walking for locomotion, and physical exercise will be assessed in the first and second study evaluations using a questionnaire that includes information on performance and duration in the week prior to the interview, according to the questionnaire adapted from the VIGITEL [33].

Blood samples from the pregnant women will be obtained in the first and second study evaluations after 8–12 h of fasting. Blood collection will be performed by a trained professional of the Health Units, by prior appointment. Fasting serum glucose and insulin levels, total cholesterol, LDL, HDL, triglycerides, and C-reactive protein will be measured. Blood glucose and lipid profile will be determined using enzymatic methods, insulin through the immunofluorometric method, and C-reactive protein using the chemiluminescence method.

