The fact that the study is unprecedented and the feasibility of the implantation of the strategy in public health services of countries of low and medium development can be considered important strengths. In addition, all the assessments will be made by trained nutritionists to ensure the quality control of the data. As all the study evaluations will be conducted in Primary Care Units, the evaluation of some newborns will be conducted after 72 h, which may affect the estimation of adiposity. To minimize this limitation, age-adjusted models will be employed [41]. We believe the results of the study will expand the knowledge regarding the effect on maternal and child health of an intervention based on the degree of food processing and on encouraging the practice of physical activity.

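### The counselling targets degree of food processing, but the dietary secondary outcome has no defined measure of energy share by processing group and no stated between-arm comparison

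*Protocol article*

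**What the plan says.** The abstract's Methods paragraph describes the intervention as "three individualized nutritional counselling sessions based on encouraging the consumption of unprocessed and minimally processed foods and the practice of physical activities". The Discussion calls it "an intervention based on the degree of food processing and on encouraging the practice of physical activity". The Interventions section gives three goals: appropriate weight gain, fresh or minimally processed foods every day, and 150 minutes of activity a week.

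The Background introduces the classification behind the dietary goal: "The NOVA food classification system classifies food according to the nature, extent, and purpose of processing". NOVA is not mentioned again in the Methods.

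The Outcomes section lists as secondary outcomes "changes in food intake, physical activity and the biochemical profile of the pregnant women". Diet is measured in two ways, both at the first and second evaluations:

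- "two 24-h recalls on non-consecutive days in each assessment", with nutrient software that "will be used to estimate the nutrients intake", followed by the Multiple Source Method for usual diet;
- "a questionnaire on the frequency of the weekly consumption of foods of interest to assess adherence".

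For continuous variables, the Statistical analyses section computes the change and tests it against baseline with a paired t-test or Wilcoxon test. The comparisons of arms on outcomes that it describes concern appropriate weight gain (relative risk) and neonatal adiposity and birth weight (correlation, then linear regression).

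**The concern.** Of the three counselling goals, two have a stated measure on the scale of the goal: weight gain in kilograms, and activity by performance and duration. For the dietary goal, the quantity named from the more detailed instrument is on a different scale. Nutrient totals can stay the same while the degree of processing changes, and the reverse.

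The stake is how the trial can be read at the end. If weight gain does not differ between arms, readers will ask whether the women's diets moved toward less processed foods at all. If no measure is fixed in advance, any processing-based measure chosen later will look chosen after the fact. In addition, a paired test within each arm does not answer a randomised question: both arms may change over pregnancy, and one arm may reach significance and the other not without any real difference between them.

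**Working it through.** The plan gives no figure to reproduce on this point. The check sets target, measure and test side by side.

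**1. Target.** The abstract, Interventions and Discussion define the dietary component by processing. The Background describes the two pregnancy studies behind the rationale in percent of energy by processing group. One compares tertiles of percent energy. The other reports 1.33 kg more gestational weight gain and 0.62 percentage points more neonatal adiposity per 1% of energy from ultra-processed diets.

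**2. What the recalls would yield as stated.** The natural measure on that scale is

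share = energy from items in the processing group / total energy from all items.

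Nutrient output gives the denominator and nutrient totals. The numerator needs a processing label on each recalled item, and no Methods section describes that labelling. The Multiple Source Method does not supply it: it models usual intake of whatever daily quantity is put in, and nutrients are the only quantity named.

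**3. What the questionnaire would yield.** It gives weekly frequency for selected foods at both evaluations, which is evidence on adherence. The article does not name the foods or tie them to NOVA groups. Turning frequency into the share above would also need energy per occasion and total energy.

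**4. What would be tested.** Write Y1 and Y2 for a dietary variable at the first and second evaluations. The stated test for continuous variables concerns the mean of Y2 − Y1 against zero, that is, against baseline. The randomised question concerns the difference between arms in Y2, given Y1. The article states no such comparison for diet, although it describes regression models for adiposity and birth weight.

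**5. Material available for a fix.** Two recalls at each of two evaluations make 2 × 2 = 4 per woman.

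- With no losses: 300 × 4 = 1,200 recalls.
- With the 20% loss assumed in the Sample size section, and all losses falling before the second evaluation: 300 × 2 + (300 × 0.80) × 2 = 600 + 480 = 1,080 recalls.

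Recalls record foods, so the information needed for coding is already planned.

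**The case against.** The strongest reply is that the article does not restrict the recalls to nutrients. It says what one software package is for, words the usual-intake step as diet, and words the outcome as food or dietary intake. Recalls hold food-level data that can be coded at any time, and a condensed article may leave such coding to a fuller document. This stands against any claim that the data could not support a processing measure. It does not remove the mismatch: the section goes as far as naming technique, software, derived quantity and usual-intake model, and the derived quantity it names is not the one the counselling targets.

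The second reply is that the questionnaire already covers adherence, and that a goal of daily consumption suits a frequency measure. This stands in part. The Interventions section sets no goal in energy share and does not mention ultra-processed products when it states the goals. The questionnaire may well show change in target foods. It does not give the share of energy by group.

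A reader might also infer three stronger things that the documents do not support.

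- *That the trial cannot show whether ultra-processed intake changed.* The questionnaire and the food-level recalls both speak against this.
- *That all the cited evidence is in percent energy.* The inpatient cross-over trial compares whole diets and reports kilograms, and the adult observational studies are cited without a metric.
- *That a processing measure would let an effect on weight be attributed to diet.* Diet and activity are randomised together as one package, so no coding of recalls can separate them, and the article states no objective to do so.

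**Conclusion.** The point holds as a mismatch between the dietary target and the stated derivation and test of one secondary outcome. No measure of energy share by processing group is defined, and no between-arm comparison of dietary change is stated. The primary outcome, the sample size and the randomised comparison of weight gain are unaffected. This is a cheap improvement worth making, not a flaw that undermines the trial.

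The conclusion assumes that the article reflects the plan on this point. If a fuller protocol or analysis plan already specifies NOVA coding and a between-arm analysis, what remains is to align the article's wording. No numerical loss can be attached, because the article gives no expected change in processing share and no variance for it.

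**What to change.** - State that each recalled food item will be assigned to its NOVA group, with a written rule for ambiguous items fixed before results are examined by arm.
- Define the dietary secondary outcome as the between-arm difference at the second evaluation, adjusted for the baseline value, in (a) percent energy from ultra-processed foods and (b) percent energy from unprocessed or minimally processed foods.
- Keep nutrient intakes and the frequency questionnaire as supporting measures, and list the questionnaire's foods with the NOVA group of each.
- Present within-arm changes from baseline as description, not as the test of the intervention's effect on diet.

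The cost is coder time for at most 1,200 recalls, and some items of uncertain group. No new visits, instruments or procedures are needed. The result would show whether the dietary target moved in the intervention arm relative to control; it would not separate the contributions of diet and physical activity.

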Blood pressure will be measured in both study evaluations with an automatic digital arm blood pressure monitor (OMRON®, model HBP 1100, Omron Health Care Inc.), using the mean of three measurements in each evaluation. Pre-gestational hypertension will be considered if the woman presents blood pressure values greater than 140/90 mmHg in the first study evaluation, or if they report the use of antihypertensive medication at the time of the first study evaluation. Those without pre-gestational hypertension that present changes in blood pressure or are using hypertensive drugs at the time of the second study evaluation will be classified as having gestational hypertension [34].

Data for fasting glucose and at one and 2 hours after 75 g glucose load at the time of gestational diabetes mellitus (GDM) screening will be obtained from the *HygiaWeb* System. For the diagnosis of GDM the criteria proposed by the World Health Organization will be adopted, which require alterations in at least one glycemic value at any time during the pregnancy: from 92 to 125 mg/dL fasting, ≥180 mg/dL 1 h after glucose load or from 153 to 200 mg/dL 2 h after glucose load [35].

The third evaluation of the study will preferably be performed at the time of the Heel Prick Test, between the third to the fifth day of life of the newborn. If this is not possible, the third evaluation will be conducted at the postpartum consultation (maximum 10 days postpartum) or at the first childcare consultation (within 15 days of life). Using a structured questionnaire, the following variables will be obtained: number of prenatal visits to the Health Unit, continuous use of medications during the pregnancy, report of chronic health problems of the puerpera, date and type of delivery, gestational age at delivery, maternal complications (hypertensive disorders and hyperglycaemia), and complications before, during and after the birth concerning the mother and the infant. Anthropometric measurements of the baby at birth will be obtained from the maternity ward discharge form.

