**Fig. 1 Fig1:**
[figure not shown]
Sequence of recruitment, intervention, and evaluation activities of the study participants. * The nutrition counselling will take place after the first evaluation of the study.

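### The gestational diabetes outcome has no post-randomisation start, so women who already meet the criterion at entry can count as events

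*Protocol article*

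**What the plan says.** The protocol article lists "complications in the pregnancy (gestational diabetes mellitus, hypertensive disorders and prematurity") among the secondary outcomes.

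For GDM, the Outcomes section says that fasting, 1 h and 2 h values "at the time of gestational diabetes mellitus (GDM) screening will be obtained from the" HygiaWeb system. The criteria adopted "require alterations in at least one glycemic value at any time during the pregnancy: from 92 to 125 mg/dL fasting", with further ranges for the 1 h and 2 h values. The gestational week of screening is not given.

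Three other statements bear on timing:

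- Eligibility and recruitment admits women at "gestational age (GA) up to 15 weeks and 6 days". On glycaemia, it says only this: "Pregnant women who report previous diabetes (or use of oral hypoglycaemic medication and/or insulin) and use of weight loss medications will be excluded".
- On blood sampling, Outcomes states: "Blood samples from the pregnant women will be obtained in the first and second study evaluations after 8–12 h of fasting". Fasting glucose is one of the analytes.
- The caption of Fig. 1 states: "The nutrition counselling will take place after the first evaluation of the study".

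For hypertension, Outcomes first identifies women who are hypertensive or on antihypertensive medication at the first evaluation. It then limits the gestational outcome: "Those without pre-gestational hypertension that present changes in blood pressure" (or use of medication) at the second evaluation.

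**The concern.** An outcome meant to show what counselling does should count events that arise after allocation. As worded, the GDM criterion covers the whole pregnancy, and up to almost 16 weeks of it may have passed before a woman is randomised. Raised fasting glucose first found in this pregnancy is not an exclusion, and no rule uses the baseline fasting sample to separate existing from new cases. The hypertension outcome makes that separation; the GDM outcome does not.

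Women already positive at entry add the same expected number of events to each arm. Randomisation balances them on average, so they do not favour either arm. They do shrink the contrast and cost sensitivity: a real effect on new GDM would look smaller than it is.

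**Working it through.** **Reading the text.** Three conditions must hold for pre-existing cases to enter the outcome.

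1. The criterion must reach back before randomisation. It covers the whole pregnancy with no start point, so it does.
2. Women who meet it early must be eligible. Only reported diabetes or glucose-lowering drugs exclude on glycaemic grounds, so they are.
3. No later rule may remove them. None is stated for GDM; one is stated for hypertension.

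**Size.** The article gives no GDM rate and no planned GDM effect, so there is no figure of its own to reproduce. The inputs below are assumptions, chosen to show the mechanism.

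- *p*: share already meeting the criterion at entry, equal in both arms, 5% to 15%.
- Incidence of new GDM among the rest: 15% control, 10% intervention. True relative risk (RR) 0.10/0.15 = 0.67; true risk difference 5.0 percentage points.

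If every entry-positive woman counts as an event:

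observed risk = *p* + (1 − *p*) × incidence

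The *p* term cancels in the difference, so observed risk difference = (1 − *p*) × true difference.

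| *p* | Control | Intervention | Observed RR | Observed difference |
|---|---|---|---|---|
| 5% | 0.05 + 0.95 × 0.15 = 0.1925 | 0.05 + 0.95 × 0.10 = 0.145 | 0.75 | 4.75 points |
| 10% | 0.10 + 0.90 × 0.15 = 0.235 | 0.10 + 0.90 × 0.10 = 0.190 | 0.81 | 4.5 points |
| 15% | 0.15 + 0.85 × 0.15 = 0.2775 | 0.15 + 0.85 × 0.10 = 0.235 | 0.85 | 4.25 points |

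**Wider inputs.** With control incidence of 10% to 20% and *p* of 5% to 20%, a true RR of 0.50 appears as 0.60 to 0.86, and a true RR of 0.70 as 0.76 to 0.91.

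**Does restriction cost more than it gains?** The Sample size section plans 300 women with 20% loss: 300 × 0.8 = 240 evaluable, or 120 per arm if allocation is 1:1 (assumed). The test is a two-sided comparison of two proportions at 0.05. Restriction leaves 120 × (1 − *p*) per arm.

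- 15% versus 10%, *p* from 5% to 15%: power is about 16% falling to 11% with entry-positive women counted, and about 21% falling to 19% after restriction.
- 15% versus 7.5% (true RR 0.50), *p* from 5% to 20%: power is 33% falling to 17% with them counted, and 43% falling to 38% after restriction.

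In each case restriction gives more power despite the smaller denominator, because it keeps the full effect size.

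**The case against.** The strongest reply concerns the data source. GDM values come from routine records of the screening test, and the phrase about any time in pregnancy can be read as describing the adopted criteria, not as an instruction to collect every glucose value. The baseline fasting sample is listed for the biochemical profile, and nothing feeds it into the GDM definition. If screening always follows randomisation, few or no pre-randomisation values would be used. This reading is possible, but the article does not state it or give the screening week. Even under it, a condition present at entry could be detected at a later test and counted as new. What stands is that the number of such cases is unknown and could be small.

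It is also fair that GDM is one of several secondary outcomes, that the Statistical analyses section specifies a relative risk only for appropriate weight gain, and that power for GDM is low in these illustrations either way. A reader might infer that this undermines a key safety or efficacy endpoint; the documents give GDM no such status.

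Restriction might seem to conflict with the stated intention-to-treat principle. It does not, provided the restricting value is obtained before randomisation: the subgroup is then fixed before allocation and the randomised comparison within it is kept. The article says that blood is drawn by prior appointment but does not place the baseline draw relative to randomisation, so that order must be confirmed.

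Finally, because the fasting and 2 h ranges have upper limits (125 and 200 mg/dL), a reader might infer that women above them are coded as having no GDM, so that the worst results become non-events. The document does not say so. It is silent on how such values are categorised, the 1 h criterion has no upper limit, and maternal hyperglycaemia is also recorded at the third evaluation. This is an ambiguity, not a shown error.

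**Conclusion.** The point holds. As written, the GDM outcome admits women who met its criterion before the intervention could act, and it differs in this from the hypertension outcome beside it. Given any true effect on new cases and a similar share of existing cases in both arms, the direction is towards no difference.

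The size cannot be found from the documents. The observed RR of 0.75 to 0.85 against a true 0.67 rests wholly on the assumed incidence and entry prevalence, and on every entry-positive woman being counted. It should be quoted only as an illustration. The primary outcome and the sample size of 300 are not touched. This should be corrected in the outcome definition, but it does not threaten the trial's main conclusion.

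**What to change.** For the analysis of this outcome, state that an event is the first qualifying value after randomisation. Then choose one of the following in advance:

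- analyse women below the plan's own fasting threshold on pre-randomisation values, taken from the baseline sample or earlier HygiaWeb records; or
- keep all randomised women and adjust for baseline fasting glucose. This keeps the full denominator, but women positive at entry can still contribute events.

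Under either option, report the number of baseline-positive women by arm, and state whether the baseline sample is drawn before allocation.

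As a minor clarification, say how values above the listed upper limits are categorised in the analysis, for example as a separately reported category. None of this alters diagnosis or care.

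The cost is a few sentences in the outcome definition and, under the first option, a slightly smaller denominator for this one outcome: 114 to 102 per arm instead of 120 for an assumed entry prevalence of 5% to 15%. Baseline glucose is already due to be measured.
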